**Introduction**

**Periodontal Disease**

All dentated individuals are susceptible to periodontal disease (1). The most common form, gingivitis, is estimated to affect up to 90% of any population (2); whilst periodontitis, more destructive in nature, affects close to 50% of the global population (2). Periodontal disease is defined as a multifactorial inflammatory process involving dysbiotic biofilm (3), a well organised colony of bacteria(1); that, if left untreated, can lead to destruction of the supporting structures of the teeth including: connective tissue, periodontal ligament fibres, and alveolar bone (4,5). The pathogenesis of this destruction is characterised by the combination of dysbiotic biofilm; commonly poor oral hygiene, time, allowing the oral biofilm or it’s bacteria to invade deeper into gingival tissues, and a hyperactive immune host response (1).

Gingivitis, the first stage of periodontal disease, initiates within 24-48hrs after ceasing toothbrushing (6). As the biofilm and its secretions are allowed to remain in contact with gingival tissues, even at this early stage the immune response is activated (7). If these bacterial deposits are allow to remain insitu, the predominately supragingival, aerobic gram-positive biofilm will slowly migrate deeper into the gingival sulcus and will, within 3 weeks, transform into a mostly anaerobic gram-negative biofilm(1,8). At this stage in the disease process, the immune response to the bacteria and their exo and endotoxins is at its most powerful releasing proinflammatory cytokines IL-1α , IL-1β, TNF-α, IL-8, IL-1ra, IL-10, and IL-12, matrix metalloproteinases (MMPs) and prostaglandin E2 (PGE_2_) as well as T and B cell lymphocytes, polymorphonuclear leukocytes (PMNs). For most individuals, the battle of bacteria and immune response remains even. However, in susceptible individuals their immune response intensifies in a way that the level of destruction outweighs repair (1,6,8).

This irreversible damage can have severe implications on quality of life (QoL) as it can involve tooth mobility and eventual loss; affecting one’s speech, eating, and causing psychological damage from fear of the judgement of others (9,10). Once destruction is evident, the condition is classified as periodontitis, the sixth most prevalent chronic condition worldwide (11). In Australia, the incidence of periodontitis is predicted to increase, with current figures showing just over 30% of the population is affected (12). Whilst the latest data shows between 1990-2019 severe periodontitis incidence has increased by 8.44% globally (13).

**Inflammation and Cardiovascular Disease**

Once triggered by periodontal disease, the immune response has systemic implications evidenced by an increase in specific inflammatory markers such as high-sensitive C-reactive protein (hsCRP) and IL-6 (14) detected in blood samples. Following the termination of tooth brushing, one study demonstrated evidence of these markers after only 21 days in healthy, young participants (mean age 23.35 ± 3.64 years) (7). The elevation of inflammatory markers, in particular hsCRP, is strongly associated with an increased risk of atherosclerosis (15), the primary cause of cardiovascular disease (CVD) (16).

Atherosclerosis is developed from matured atherosclerotic plaque forming on blood vessel walls (17). This fibro-lipid structure consists of key immune inflammatory cells and markers such as leukocytes, cytokines, chemoattractants, and MMPs (18). Inflammation as such has been identified as being heavily involved in all stages of atherosclerosis formation (19). Oral biofilm is also recognised as an influencing factor (18,20) and has been speculated to initiate or promote atherosclerotic plaque formation. Resulting from the bacterial challenge in the oral cavity, vasodilation in gingival tissues (1) allows the virulent bacteria, their toxins as well as the induced proinflammatory mediators easy access to body organs and systems via the bloodstream (4,5,21,22). Once transported, they can influence or cause harm to susceptible tissues and introduce localised inflammatory responses elsewhere in the body (23) and as such, as well as CVD (21) are linked to stroke (20), Alzheimer’s disease, diabetes, and cancer (5).

Patients living with CVD are at a high risk of having a cardiac event with even the slightest elevation of inflammatory markers (24,25) and have an increased risk of recurrent cardiovascular events, including death after surviving a myocardial infarction (MI) (26). In 2021, CVD (ICD20-ICD25) was the leading cause of death in Australia (27) and is responsible for 32% of deaths and 38% of premature deaths globally (28). Due to the increased systemic inflammation caused by periodontal disease (29), CVD patients who are also suffering with periodontal disease, have a further elevated risk of a future cardiac event. Therefore, it is integral to reduce the inflammatory comorbidity of periodontal disease to help prevent poor CVD outcomes.

**Prevention**

Primary prevention of periodontal disease

The most important and effective way to prevent periodontal disease is with an optimal oral hygiene routine (30), followed by regular dental check-ups and hygiene appointments, as well as the absence or control of modifying risk factors such as smoking (31), and diabetes (32). Poor oral hygiene habits, defined as never or rarely brushing teeth, have been shown to increase the risk of a CVD event significantly (HR 1.7, 95% CI 1.3 to 2.3; P<0.001) (33), whilst incorporating just one toothbrushing session per day is associated with a 9% risk reduction of a CVD event (34). The recommended ideal oral hygiene routine includes brushing twice a day for at least two minutes with a fluoridated toothpaste (35,36), preferably with an electric oscillating/rotating power toothbrush (37–39). As adjunct, as toothbrushes cannot reach all tooth surfaces, particularly in between the teeth, interdental cleaning products such as interdental brushes should be used before brushing at least once daily (40–42).

Essential to good oral hygiene and the prevention of oral disease, is education (43). Involving CVD patients after having a MI, a randomised controlled trial (RCT) attempted to introduce an intervention directly to patients in a cardiology ward (44) as a way of lowering their future CVD event risk. However, due to a lack of awareness of the importance of oral health for cardiovascular health, recruitment has been low. It is reasonable that there is a lack of understanding of the importance of oral health for cardiovascular health. Currently, the most easily accessible health information regarding ways to reduce risk factors attaining to CVD only includes smoking cessation, reducing alcohol intake, improving diet, and becoming physically active (28,45–49). Unless specifically searched for, the importance of good oral hygiene for cardiovascular health is never mentioned.

**Oral health promotion studies**

Australians have a universal right to all areas of healthcare (50), and should have access to any health services needed, whenever and wherever they are required (51). However, oral health is not a priority within hospital wards currently, and there is no plan to incorporate an oral health practitioner (OHP) into routine care in hospitals as part of Australia’s National Oral Health Plan 2015–2024 (52). Oral care is a part of standard care within hospitals, and when appropriately completed, it has shown to reduce secondary illness incidence (53). Traditionally, oral health care and education is provided by an OHP. However, in hospitals this is designated to nurses who have many barriers to overcome to deliver oral health education, such as: a lack of training, time or resources, to name just a few (54–56). Additional obstacles can present from patients, especially if oral health is not a priority to them; but can also derive and can come from the hospital organisations themselves (55). OHPs as such, are an appropriate alternative to take on this responsibility and could help to eliminate barriers, alleviate the workload of nurses, and improve oral health knowledge by delivering education directly to patients, providing access to resources, and, if required, refer for any urgent oral care (57).

Many interventional studies regarding oral care interventions have been conducted residential aged care facilities (RACF) (58–61). One 6-month study placed an OHP within five RACFs on the Central Coast, NSW, Australia, and trialed a program that included individualised oral health risk assessments, health care plans, oral hygiene instructions, and referral for extensive dental treatment when necessary (62). Additionally, an informal oral health training was provided to all RACF staff members. The positive health outcomes demonstrated by this 6-month interventional study, known as ‘Senior Smiles’, have resulted in the immediate incorporation of this concept in two RACFs and the number of further RACFs adopting this concept is continuously growing (63).

Conversely, at present, only minimal oral health interventions have been conducted within hospital wards, clinics, or outpatient facilities. Those that have been conducted mainly involve the education of nurses (53,64–66), but are not empowering patients. The limited literature available regarding oral health interventions direct to patients include: a cardiology ward pre- and post-heart surgery (67), a stroke ward (68), and a diabetic outpatient clinic (69). Interestingly most oral care intervention studies have been conducted within mental health wards (70–73). Interventions within a cardiac rehabilitation out-patient facility exist, however they are only related to self-reported oral health knowledge and behaviour (74,75). Currently, there are no known interventions clinically monitoring the oral hygiene status of CVD patients in a cardiac rehabilitation out-patient setting.

The use of digital media has been proven effective as a strategy to improve patient’s knowledge and confidence regarding their health condition (76,77), even in individuals with low literacy levels (78,79). Additionally, digital media based education strategies in the dental clinic waiting room have shown to improve self-reported oral hygiene habits (80). However, to the best of our knowledge, there are no published studies seeking to improve oral health knowledge, motivation, and confidence by using a digital education approach in a cardiac rehabilitation setting. The aim of this study is to assess whether incorporating an individualised oral hygiene instruction (OHI) partnered with a digital oral health education (DOHE) package can improve oral hygiene and clinic oral health of CVD patients in cardiac rehabilitation out-patient facilities.

The primary outcome of this study is to determine if individualised OHI combined with DOHE improves approximal plaque index (API) (81) scores between baseline and the 6-week follow-up, compared with usual care/no OHI education. Secondary outcomes of this study will determine if digitally delivered oral health education alone or partnered with individualised OHI improves API scores between baseline and the 12-week follow-up, compared with usual care. It will compare the mean reduction of API and SBI between each group at baseline and follow up, and determine if any participant reaches scores that are clinically significant. It will assess any changes to patients’: motivation, confidence, and behaviour regarding their oral hygiene practices, knowledge of oral health impacts on cardiovascular health, as well as their experience with oral care whilst on the ward. Additionally, it will assess the cardiac nursing staff views on an oral health education program within the rehabilitation facility. As good oral hygiene habits are an upstream approach of reducing risk of systemic chronic inflammation, and as such, risk of a future cardiac event (29), we hypothesise introducing an individual OHI partnered with DOHE program into the cardiac rehabilitation out-patient clinic will help improve API scores between baseline and follow-up. We also hypothesise the program will increase patients’ awareness of the impact of oral health on cardiovascular health and help to motivate and give them confidence in caring for their oral health; and if not doing so already, incorporating regular visits to an OHP.

**Methods**

Study Design

A dual-center, single-blind (examiner), parallel design randomised control trial of 165 patients attending an outpatient cardiac rehabilitation center within two public hospitals in Sydney, Australia. See **Figure 1.** for study flow diagram. The intervention populations will receive either a tablet-delivered specifically selected series of advertisement free, web-based educational videos covering multiple CVD and oral health related topics alone or partnered with individually tailored OHI. The control population will receive usual care as detailed below. The examiner will be blinded to the group allocation.

Patient population

The study population will be patients presenting to the outpatient cardiology rehabilitation centre participating in the Cardiac Education and Assessment Program (CEAP) at Westmead and Blacktown public hospitals, Sydney Australia. CEAP provides personalised support, exercise and education to help strengthen patient’s hearts after having a cardiovascular event and helps to lower risk of a future cardiovascular event (82). These patients attend due to a range of heart conditions such as coronary heart disease, heart failure, and those waiting for, or who have had a heart transplant. Due to the variety of heart conditions and co-morbidities, patients are placed on either a 6-week or 12-week program and can attend once or twice weekly. As these patients have taken part in this program, prioritising their cardiovascular health, and showing a motivation to reduce future risk of a cardiovascular event, we predict these patients will be interested in receiving education regarding oral health impacts on CVD.

Participant eligibility

A total of 165 participants will be recruited at either Westmead or Blacktown outpatient cardiac rehabilitation clinics who are attending as part of the CEAP program. Patients 18 years or older with a recent diagnosis of CVD , recent myocardial infarction and/or recent hospitalisation resulting from CVD will be approached for screening. This will include a clinical examination consisting of periodontal screening and recording (PSR), API, and sulcus bleeding index (SBI) (83) will be completed, followed by a self-report questionnaire. Patients will be excluded if:

- they have been diagnosed with heart failure.
- have/are waiting for a heart transplant,
- are too physically or mentally unwell on the day.
- have a cognitive impairment.
- who do not speak or have limited language skills in English.

If they have visited an OHP for treatment of gum disease (supra- and/or subgingival scaling and root planning) in the last 6 months,

- have an API score of ≤59%
- are edentulous.

A study researcher will ensure that eligibility criteria are satisfied before approaching the participants by viewing their clinical records. Part of discussing the study with participants will allow the researcher to determine if they are edentulous or have seen an OHP within the last 6 months which will exclude them before the baseline assessment. A sequence of the recruitment process is provided in **Fig 2**.

Recruitment and consent

Eligible patients will be recruited either before or after their CEAP session in the cardiac rehab clinic. A trained oral health therapist will explain the study to potential participants. Electronic consent forms will be provided on iPads provided by the study, being hosted on Western Sydney Local Health District (WSLHD) Research Electronic Data Capture (REDCap) (84). As such the participant must complete written/electronic consent before being able to progress to the clinical examination (API, SBI and PSR) and data collection stage. Ethical approval will be obtained via: Western Sydney Local Health District Human Research Ethics Committee (HREC). This trial will be registered on the Australian New Zealand Clinical Trails Registry.

Randomisation

Randomisation will be stratified by age and site. A randomisation allocation table will be computer generated and REDCap will be used for allocation of participants to each group. Participants will be randomised at the end of the self-report questionnaire and randomised into a 1:1:1 ratio into one of three arms of the study. Due to the nature of the interventions within the trial, participants cannot be blinded.

Interventions

Participants will be randomised into one of 3 arms as follows: Group A) individualised OHI combined with an oral health video package, Group B) oral health video package only, and Group C) usual care without any oral health education given. At the final follow up, after completing clinical measurements and the follow-up questionnaire, Group B and Group C will be given tailored OHI and Group C will also be shown the video package to ensure all participants have received the comprehensive oral health educational package after completion of the study. A single calibrated and trained oral health therapist, blinded to the treatment allocations will perform the baseline and follow up assessments on all participants. After the initial assessment, if any obvious dental issues (without the use of radiographs) are detected, patients will be given a letter that can be taken to a dental practitioner for further investigation.

Oral hygiene instruction

Trained research assistants, oral health therapy and/or dental students will deliver tailored OHI, using API and SBI results from the assessment as a guide for patient focus. Toothbrushing or interdental cleaning instructions will be given in accordance with the oral hygiene standard operating procedure (SOP). See separate document.

Video packages

Videos to be included in the oral health education package will be evaluated and rated by a multi-disciplinary panel to ensure content validity and consumer engagement. The intervention video package will include short clips in relation to oral health and CVD, as well as oral hygiene practices. (77). The videos included will be advertisement free; and created by either government bodies, or relevant health bodies such as the Australian Dental Association (ADA). These will be delivered to participants in Group A and Group B once the self-report form has been completed at baseline, and Group C at the final visit, embedded within REDCap.

**Study outcomes**

Primary outcome

The primary outcome of this study is to show the percentage of participants reducing their API score ≥40% after 6 weeks, compared to baseline is higher in Group A than in Group C.

Secondary outcomes

The secondary outcomes of the study will be:

- To show the percentage of participants reducing their API score by ≥40% after 12 weeks, compared to baseline, is higher in Group A (OHI & DOHE) than in Group C (usual care/no oral hygiene intervention).
- To show the reduction in mean API score after 6 weeks, compared to baseline, is higher in Group A (OHI & DOHE) than in Group C (usual care/no oral hygiene intervention).
- To show the reduction in mean API score after 12 weeks, compared to baseline, is higher in Group A (OHI & DOHE) than in Group C (usual care/no oral hygiene intervention).
- To show the reduction in mean API score after 6 weeks, compared to baseline, is higher in Group A (OHI & DOHE) than in Group B (DOHE).
- To show the reduction in mean API score after 12 weeks, compared to baseline, is higher in Group A (OHI & DOHE) than in Group B (DOHE).
- To show the reduction in mean API score after 6 weeks, compared to baseline, is higher in Group B (DOHE) than in Group C (usual care/no oral hygiene intervention).
- To show the reduction in mean API score after 12 weeks, compared to baseline, is higher in Group B (DOHE) than in Group C (usual care/no oral hygiene intervention).
- To show the reduction in mean SBI score after 6 weeks, compared to baseline, is higher in Group A (OHI & DOHE) than in Group C (usual care/no oral hygiene intervention).
- To show the reduction in mean SBI score after 12 weeks, compared to baseline, is higher in Group A (OHI & DOHE) than in Group C (usual care/no oral hygiene intervention).
- To show the reduction in mean SBI score after 6 weeks, compared to baseline, is higher in Group A (OHI & DOHE) than in Group B (DOHE).
- To show the reduction in mean SBI score after 12 weeks, compared to baseline, is higher in Group A (OHI & DOHE) than in Group B (DOHE).
- To show the reduction in mean SBI score after 6 weeks, compared to baseline, is higher in Group B (DOHE) than in Group C (usual care/no oral hygiene intervention).
- To show the reduction in mean SBI score after 12 weeks, compared to baseline, is higher in Group B (DOHE) than in Group C (usual care/no oral hygiene intervention).
- Assess the percentage in each Group that has reached clinically significant API scores of ≤35%.
- Assess the percentage in each Group that has reached clinically significant SBI scores of ≤25%.
- Assess the percentage in each Group that has reached clinically significant API scores of ≤35% as well as a clinically significant SBI scores of ≤25%.
- Improved oral hygiene habits as reported by an increase in brushing frequency and/or inclusion of interproximal cleaning, comparing baseline to follow-up.
- Improved understanding between the link between heart health and oral health (Likert scale). A yes response increase of ≥ 5 out of 12 will be considered as an improved understanding.
- Confidence to improve oral hygiene habits with a self-reported 5-point Likert scale. A change in response from neutral, disagree or strongly disagree to agree or strongly agree compared to baseline will be considered confident.
- Motivation to improve their oral health and see an OHP regularly with a yes/no response and a self-reported 5-point Likert scale. Answer change from no to yes will be considered motivated to improve their oral health and a response of: ‘Yes I have made an appointment since the assessment’ or ‘Yes, however I have not yet made an appointment’ will be considered motivated to visit an OHP regularly.
- Patient perceptions of a nurse’s role in their oral health care using yes, no answers. Answering yes will be considered cardiac nurses can play a role in their oral health.
- Cardiac nurse perception of the importance and effectiveness of the intervention in the rehab setting (Likert scale). A response of 4 or 5 will be considered as the intervention being important and effective.

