**Sample size**

The required sample size for this study is calculated to be a total of 165 (1:1:1 Group A: Group B: Group C). This calculation includes provision for a 10% attrition rate, two tailed tests, type 1 error of 5%, and will have 80% power to detect any significant difference between Group A and Group C. This calculation is based from an API score reduction of 25% in the intervention arm of Ziebolz, et al 2009 study (87). However, due to our exclusion criteria of ≤59% API score, we will expect to see a 40% decrease in Group A, compared to 15% in Group C. This current study is powered to detect a difference in percentage proportion of those between Group A and Group C however, has poor power to detect a difference between Group B and Group C.

| Table 2. Adapted API/SBI measurement results (88) | | |
| --- | --- | --- |
|  | **API** | **SBI** |
| Poor oral hygiene | >35% | >25% |
| Fair oral hygiene | 35% | 15-25% |
| Good oral hygiene | <25% | <15% |

| Table 3. Adapted PSR code definitions (86,89). | |
| --- | --- |
| Code | Clinical Signs |
| 0 | Absence of clinical signs: no calculus, or BOP  Coloured band on WHO probe completely visible. |
| 1 | No calculus.  BOP  Coloured band on WHO probe completely visible. |
| 2 | Supra and/or subgingival calculus  BOP  Coloured band on WHO probe completely visible. |
| 3 | Periodontal pocket 3.5mm-5.5mm  Coloured band on WHO probe partially visible |
| 4 | Periodontal pocket >5.5mm deep  Coloured band on WHO probe no longer visible |
| X | Sextant absent of dentition |
| * | Periodontal abnormalities which include:  Furcation involvement  Mobility  Mucogingival problems for example: exudate, severe oedema  >3.5mm recession  The * is recorded next to the sextant number code. E.g. “3*” |

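### The primary outcome and sample size rest on an unexplained ≥40% API cut while the stated primary analysis is of API scores, so the 80% power does not describe that analysis and the cut probably discards information.

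*Protocol*

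**What the plan says.** **Outcome.** Under Study outcomes, the primary outcome is to show that "the percentage of participants reducing their API score ≥40% after 6 weeks, compared to baseline is higher in Group A than in Group C". Whether 40% is relative to baseline or in percentage points is not stated. The comparison of means for the same arms and visit is secondary: "To show the reduction in mean API score after 6 weeks, compared to baseline, is higher in Group A (OHI & DOHE) than in Group C". Another secondary outcome reads "Assess the percentage in each Group that has reached clinically significant API scores of ≤35" per cent, and Table 2 puts API above 35% in the poor category. Patients with API of 59% or less are excluded.

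**Sample size.** The number is "calculated to be a total of 165 (1:1:1 Group A: Group B: Group C"), with "provision for a 10% attrition rate, two tailed tests, type 1 error of 5" per cent, and the trial "will have 80% power to detect any significant difference between Group A and Group C". The section expects a 40% decrease in Group A and 15% in Group C, then says: "This current study is powered to detect a difference in percentage proportion of those between Group A and Group C". The 40% is derived from a 25% API reduction in a cited study, raised because of the baseline exclusion. That supports an expected effect; it is not offered as a reason for a responder definition.

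**Analysis.** The Statistical analysis section makes an adjusted analysis of variance on API scores the primary analysis, with baseline API in the model. The chi-squared test for binary outcomes appears only as part of the unadjusted analysis. The last paragraph of the introduction states the primary outcome as an improvement in API scores at 6 weeks, with no cut.

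**The concern.** API is a 0–100% score recorded at baseline and 6 weeks, and the primary outcome reduces it to yes or no. A fall just short of the cut then counts the same as no fall, and one just past it the same as a very large one. Such a loss can be worth accepting when the cut marks a clinically meaningful state, but the Protocol does not argue this for 40%.

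The Protocol also places its primary question on two scales: outcome and sample size are binary, while the primary analysis and the introduction's wording concern the score. A reader cannot tell which result decides the trial, and the stated power applies to only one of the two.

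**Working it through.** **1. Reproduce the sample size.** Inputs from the Sample size section: "two tailed tests, type 1 error of 5" per cent, 80% power, 10% attrition, and 40% vs 15% read as responder proportions (p̄ = 0.275).

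n = [1.960·√(2·0.275·0.725) + 0.842·√(0.40·0.60 + 0.15·0.85)]² / 0.25² = 48.9, so 49 per arm.
49 / 0.90 = 54.4, so 55 per arm; 3 × 55 = 165. This matches exactly, so the trial was sized on the responder comparison.

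Power at 49 per arm: the null SE is √(2·0.275·0.725/49) = 0.0902 and the alternative SE is √(0.3675/49) = 0.0866. Φ[(0.25 − 1.960·0.0902)/0.0866] = Φ(0.845) = **80.1%**.

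**2. Same participants, mean change.** No SD is given, so a distribution must be assumed. If API change is normal with equal SDs, having 40% and 15% above one cut implies d = z(0.85) − z(0.60) = 1.036 − 0.253 = 0.783. The noncentrality is 0.783·√(49/2) = 3.88, and a two-sided t-test on 96 df has **97.0%** power (97.2% by the normal approximation).

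**3. Unequal SDs.** Let k = SD(A)/SD(C), keep 40% and 15% above the cut, and set SD(C) = 1. The mean difference is 1.036 − 0.253k, its SE is √((k² + 1)/49), and power is Φ(difference/SE − 1.960):

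| k | Difference | SE | Power, means |
|---|---|---|---|
| 0.8 | 0.834 | 0.183 | 99.5% |
| 1.0 | 0.783 | 0.202 | 97.2% |
| 1.25 | 0.720 | 0.229 | 88.2% |
| 1.5 | 0.656 | 0.258 | 72.2% |
| 2.0 | 0.530 | 0.319 | 38.1% |

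The responder test stays at 80.1% throughout.

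**4. Two-class response.** Suppose participants either change their habits or do not, and the arms differ only in the share who change, set to give 40% vs 15% at or above a 40-point fall. Simulation, 49 per arm, all settings assumed:

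| Non-changers, mean (SD) | Changers, mean (SD) | SD ratio A/C | Cut | t-test |
|---|---|---|---|---|
| 5 (15) | 55 (8) | 1.22 | 81% | 71% |
| 10 (15) | 50 (5) | 1.17 | 81% | 67% |
| 5 (20) | 50 (6) | 1.14 | 81% | 65% |

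**5. The other reading of 40 and 15.** If these are mean falls (a difference of 25 points), t-test power at 49 per arm depends on the unstated SD: 98% at SD 30, 94% at 35, 86% at 40 and 78% at 45. With a cut at 40 points, the responder test would have 88%, 78%, 67% and 57%.

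**6. The cut against the 35% level.** On the relative reading, a fall of exactly 40% reaches 35% only from a baseline of 35/0.60 = 58.3% or less, just below the entry limit; from 60% it ends at 36%, and from 80% at 48%. On the points reading, a 40-point fall reaches 35% from any baseline up to 75%: 60% ends at 20%, 80% at 40%. Whether a minimal responder reaches the level the Protocol calls clinically significant therefore depends on the reading and the starting score.

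**The case against.** The best counter-argument is that the Protocol already plans nearly what is asked for. Its primary analysis is a baseline-adjusted comparison of API scores, so a reader who infers that the confirmatory test is the dichotomised one goes further than the text allows. That stands. It also exposes the sharper fault, because outcome and sample size are then out of step with the analysis.

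Secondly, a reader might take 80% against 97% as a plain fact. The documents do not support this. They give no SD, the score is bounded, and participants are selected for high baseline API. For a behavioural intervention a two-class response is plausible, and there the cut does better even at SD ratios of 1.14 to 1.22. It would be wrong to say that the advantage reverses only when Group A is much more variable.

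Thirdly, a reader might infer an underpowered trial. It is not: 165 is correct for the responder comparison, and 80% is conventional. Nor does a loss of power for Group B vs Group C follow, since no ≥40% comparison is listed for that pair; their API comparisons are of means.

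Finally, a mean change has no clinical anchor of its own, and on the relative reading the cut lands close to 35% for those near the entry limit. Both points are fair. They weaken any claim that the cut is unrelated to the 35% level, but they do not supply the missing justification.

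**Conclusion.** The concern holds in this form: the ≥40% cut is unexplained, and the primary outcome and sample size are on a different scale from the stated primary analysis, so the 80% power does not describe that analysis. This rests on the text alone.

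The cut also discards information, and the probable cost is material: 80.1% against about 97% power at 49 per arm if changes are roughly normal with similar SDs. That is one scenario. The mean comparison has about 88% at an SD ratio of 1.25, 72% at 1.5, and 65–71% in the two-class settings shown. None of these figures credits adjustment for baseline API. The matter is one of coherence and likely lost efficiency; the design is not invalid. It should be corrected.

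**What to change.** - Define the primary outcome as mean API at 6 weeks (change from baseline), Group A vs Group C, analysed with the baseline-adjusted model already in the Statistical analysis section. Align Study outcomes and the introduction with it.
- Keep the ≥40% responder rate as a supportive secondary outcome beside the 35% outcome, and say whether 40% is relative or in points.
- Restate power in the Sample size section for the mean difference, over a range of assumed SDs. Keep 165 participants.

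The cost is a wording amendment to the protocol and registration, made before unblinded data are seen; no new participants, visits or measurements are needed. The downsides are that the headline becomes a mean difference, and that power could fall below that of the cut if response is strongly two-class or Group A is clearly more variable.
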